## Abstract

**Background:**

Blood pressure has become one of the most important vital signs to monitor in the perioperative setting. Recently, the Italian Society of Anesthesia Analgesia Resuscitation and Intensive Care (SIAARTI) recommended, with low level of evidence, continuous monitoring of blood pressure during the intraoperative period. Continuous monitoring allows for early detection of hypotension, which may potentially lead to a timely treatment. Whether the ability to detect more hypotension events by continuous noninvasive blood pressure (C-NiBP) monitoring can improve patient outcomes is still unclear. Here, we report the rationale, study design, and statistical analysis plan of the niMON trial, which aims to evaluate the effect of intraoperative C-NiBP compared with intermittent (I-NiBP) monitoring on postoperative myocardial and renal injury.

**Methods:**

The niMon trial is an investigator-initiated, multicenter, international, open-label, parallel-group, randomized clinical trial. Eligible patients will be randomized in a 1:1 ratio to receive C-NiBP or I-NiBP as an intraoperative monitoring strategy. The proportion of patients who develop myocardial injury in the first postoperative week is the primary outcome; the secondary outcomes are the proportions of patients who develop postoperative AKI, in-hospital mortality rate, and 30 and 90 postoperative days events. A sample size of 1265 patients will provide a power of 80% to detect a 4% absolute reduction in the rate of the primary outcome.

**Conclusions:**

The niMON data will provide evidence to guide the choice of the most appropriate intraoperative blood pressure monitoring strategy.

**Clinical trial registration:**

Clinical Trial Registration: NCT05496322, registered on the 5^th^ of August 2023.

## Background

In the last 50 years, anesthesia-related mortality has decreased dramatically [1], with a European in-hospital mortality rate after noncardiac surgery of 4% [2]. The relationship between intraoperative arterial blood pressure targets and serious perioperative complications is of critical importance in perioperative medicine. Hypertension and hypotension can affect the function of vital organs such as the brain, heart, and kidneys, and recent studies have demonstrated associations between low mean arterial pressure (MAP), organ injury, and 30-day mortality [3–9]; however, this finding has been questioned by a recent meta-analysis [10]. Blood pressure (BP) has become one of the most important vital signs to be monitored in the perioperative setting. Recently, the Italian Society of Anesthesia Analgesia Resuscitation and Intensive Care (SIAARTI) recommended, with a low grade of evidence, continuous BP monitoring during the intraoperative period [11]. Although BP assessment is mandatory and part of the standard monitoring in the perioperative setting, there is currently no consensus on specific BP targets for different surgical patient populations. Furthermore, the depth of hypotensive events per se and the total time spent in hypotension can be associated with worse outcomes [8, 12].

In recent years, there has been a trend toward keeping MAP higher than 65 mmHg to reduce postoperative complications [8]. A personalized intraoperative BP management strategy, considering the individual patient’s preoperative BP, showed an improvement in postoperative outcomes [13]. This strategy is still debated compared to those based on absolute intraoperative MAP thresholds [9].

Intraoperative blood pressure is usually measured intermittently using non-invasive oscillometric devices (I-NiBP) every 3–5 min, potentially leading to unrecognizable periods of hypotension [14]. Less than 5 min of MAP less than 55 mmHg during noncardiac surgery is independently associated with an increased risk (30%) of postoperative acute kidney injury (AKI) and myocardial injury [8]. On the contrary, continuous monitoring allows early detection of hypotensive events and probably a prompter treatment. Commonly, invasive blood pressure monitoring, which provides continuous blood pressure, is used in selected patients at high risk of complications and/or major surgeries. In patients at lower risk, continuous non-invasive blood pressure (C-NiBP) monitoring with the finger-cuff method may be of potential benefit. These devices adopt the volume-clamp [15, 16] method and the physiocal algorithm for continuous BP estimation (ClearSight® Edwards Lifesciences Corp, Irvine, CA), using a cuff wrapped around the middle phalange of the finger. Evidence suggests that arterial pressure measurements from this monitor are comparable to invasive blood pressure monitoring [17–19] and non-inferior to conventional automatic oscillometric methods [20].

The use of C-NiBP monitoring is associated with a shorter duration of intraoperative hypotension and hypertension compared to conventional intermittent blood pressure monitoring [21–23]. Chen et al. demonstrated that using C-NiBP devices for every hour of surgery, an average of 14 min of potentially treatable hypotensive events [13]. Whether the ability to detect more hypotension events by C-NiBP monitoring can improve patients’ outcomes is still unclear. Therefore, we designed a randomized trial to evaluate the effect of intraoperative C-NiBP compared with I-NiBP monitoring on postoperative myocardial injury.

## Main text

### Objectives

We hypothesize that C-NiBP monitoring could reduce postoperative complications, decreasing the duration and number of intraoperative hypotension events. The primary aim of the Continuous vs intermittent Non-Invasive blood pressure MONitoring (NiMon) trial is to evaluate whether the use of C-NiBP as compared to I-NiBP monitoring during the intraoperative period decreases the proportions of patients who develop myocardial injury in the first postoperative week.

### Trial design

The niMon trial is an investigator-initiated, multicenter, international, open-label, parallel-group, randomized clinical trial.

## Methods

### Study setting

Potential participants will be screened in Europe and recruited in participating centers by the local investigators. Each participating center will be coordinated by a local principal investigator who is responsible for trial activities, local monitoring, and adherence to regulations at each site. The complete recruiting centers list is reported on the trial website (http://www.nimontrial.it).

### Eligibility criteria

#### Inclusion criteria

All adult (age ≥ 18 years) patients scheduled for elective noncardiac;Surgical cases planned with non-invasive BP monitoring according to local clinical practice or policies.

#### Exclusion criteria

Missing preoperative serum creatinine during the 30 days prior to surgery;Preoperative dialysis;Chronic kidney disease (eGFR < 60 ml/min Cockcroft-Gault equation);Surgical procedure with expected duration lasting less than 60 min;Planned use of permissive hypotension;Nephro/urological procedures (including nephrectomy and renal transplantation, pheochromocytoma surgery);Raynaud’s syndrome; andRefusal to give informed consent.

### Intervention description

During the 30 days before a scheduled surgery, all patients will be screened for inclusion criteria, and reassessed the day of surgery; after obtaining written informed consent, the patients will be randomized to a blood pressure measurement strategy (C-NiBP or I-NiBP), once arrived in the operating room. Thereafter, patient monitoring is completed according to local policy. Patients may receive general or regional anesthesia according to the preferences of the attending anesthesiologist, using the drugs commonly used in local practice.

Mechanical ventilation, when necessary, is delivered with the use of a tidal volume of 6–8 ml/kg predicted body weight and a PEEP level between 5 and 8 cmH_2_O. The FiO_2_ is adjusted to obtain an oxygen saturation > 95%. The respiratory rate is set to maintain end-tidal carbon dioxide between 30 and 35 mmHg. The core temperature should be maintained at least 36 °C. In each group, patients receive balanced crystalloid solutions at 3–5 ml/kg per hour as maintenance fluid during surgery. In both groups, the fluid balance is titrated by the attending physician, according to local good practice. In both groups, every hypotensive event (*defined as MAP* < *65 mmHg for at least 1 min*) should be promptly treated, with the most appropriate treatment as decided by the attending anesthetist. At any time, the treating physician could choose to start invasive arterial BP monitoring.

### Outcomes

The study has one primary and several secondary outcomes that are described below.

#### Primary outcome

Proportions of patients developing myocardial injury after noncardiac surgery (MINS) in the first postoperative week.*Definitions*: elevation of serum troponin T (TnT) >= 30 ng/L or high-sensitivity troponin T (hsTnT) >20 ng/L to <65 ng/L with an absolute change of ≥5 ng/L from baseline, or a high-sensitivity troponin T concentration ≥65 ng/L in the first postoperative week

#### Secondary outcomes

Proportions of patients who develop postoperative AKI in the first postoperative week.*Definition:* increase in postoperative serum creatinine concentration during the first 7 postoperative days by more than 1.5-fold or greater than 0.3 mg/dl or urine volume < 0.5 mL/kg/h for 6 h. Baseline creatinine concentration was defined as the most recent recorded measurement within 30 days before the surgery.In-Hospital Mortality*Definition: Death for any-cause during postoperative hospital stay*Proportion of severe clinical events occurring within the 30 days following surgery*Definition: Stroke, Nonfatal cardiac arrest, AKI Stage 2–3, Sepsis, Death*Proportion of severe clinical events occurring within the 90 days following surgery*Definition: Stroke, Nonfatal cardiac arrest, AKI Stage 2–3, Sepsis, Death*

### Assignment of interventions

Eligible patients will be randomized in a 1:1 ratio to receive C-NiBP or I-NiBP as an intraoperative monitoring strategy. A computer-generated permuted block randomization list with varying block sizes will be concealed and created by a statistician. Randomization will be implemented using a web-based electronic system incorporated in the electronic case report form to ensure allocation concealment. Randomization will be stratified according to the patient cardiovascular perioperative risk (RCRI). Trial intervention is not blinded for investigators in the operating room and patients because blinding to intraoperative blood pressure monitoring is unfeasible. The statistician will be blinded to allocation. Clinical outcomes will be recorded by personnel blinded to patient allocation according to planned timepoints (preoperative, intraoperative, daily up to 7 days following surgery, hospital discharge, 30 and 90 days following surgery).

## Data collection and management

This study will use Research Electronic Data Capture (REDCap), owned by the SIAARTI, for data collection, transmission, and storage. All study data will be entered via a 2-factor password-protected website. REDCap servers are hosted in a data center inside the European Union, and all web-based information transmission is encrypted. The study data manager will assess the quality of the data (validation of range and consistency). At the end of each center's enrollment period, specific queries will be sent to each center by the study's data manager, along with the members of the Steering Committee. After recording all entries and clarifying all queries, the database will be closed before the data analysis.

### Sample size

Previous data indicate that the incidence of myocardial injury after noncardiac surgery (MINS), according to the definition of TnT elevation > 30 ng/L, is 7.9% [24]. We calculated that the enrollment of 602 patients per group (total: 1204 patients) would provide 80% power to detect a 4% absolute reduction (50% relative risk reduction, number needed to treat of 25) in the primary outcome rate in either the C-NIBP or I-NIBP group, with an alpha level of 0.05. In the occurrence that most centers will have employed the high sensitivity troponin assay (MINS incidence 17%) [25], we plan to evaluate the appropriateness of the sample size during the interim analyses, considering the incidence of the primary outcome.

The attrition rate is expected to be less than 5% and likely due to protocol violations, crossover, and drop-outs. We plan to enroll a total of 1265 patients in 24 months.

### Statistical method, analysis strategy, subgroup analysis

The Kolmogorov–Smirnov test and histogram visualization will be used to evaluate the distribution of the variables and descriptive statistics, including mean (± standard deviation) or median and interquartile range, will be presented based on the skewness of the distribution. Categorical variables will be presented as proportions. Comparison between groups will be conducted using Student’s *t* test for normally distributed continuous variables, the Mann–Whitney-Wilcoxon nonparametric test for non-normally distributed variables, and the chi-square test or Fisher’s exact test for discrete variables. A preplanned subgroup analysis will be performed on the surgical risk stratification (RCRI), fluid balance strategy, and hypertension history. All analyses will be performed on an intention-to-treat (ITT) basis. All statistical tests will be two-sided and assume a significance α-level of 0.05.

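### Randomization is stratified by RCRI, but the only test named for the binary primary outcome is unstratified: valid, slightly conservative, and free to improve

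*Protocol article*

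**What the plan says.** Under Assignment of interventions, the article states: "Randomization will be stratified according to the patient cardiovascular perioperative risk (RCRI"). No other stratification factor is named.

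The primary outcome is a proportion: patients with myocardial injury in the first postoperative week, with separate thresholds for conventional and high-sensitivity troponin T.

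The section on statistical method lists tests by type of variable. For a binary outcome the list gives "the chi-square test or Fisher’s exact test for discrete variables". It adds "All statistical tests will be two-sided and assume a significance α-level of 0.05". RCRI returns only as one of three preplanned subgroup factors. No adjustment for RCRI or troponin assay is stated.

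Under Sample size, "the enrollment of 602 patients per group (total: 1204 patients") "would provide 80% power to detect a 4% absolute reduction". The planning incidence is 7.9% for conventional troponin T and 17% if most centers use the high-sensitivity assay. The Abstract says that the article reports the statistical analysis plan.

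**The concern.** Stratified randomization makes the arms nearly equal within each RCRI level, so differences between levels hardly contribute to the treatment contrast. An unstratified chi-square test computes its variance as if they did. If RCRI predicts myocardial injury, the standard error is a little too large, the true type I error falls below 0.05, and some power is lost with nothing gained in return.

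What is at stake is precision in the primary comparison. The interim stopping rule is also affected: it sets a threshold of p < 0.01 without naming a test, so by default it would use the same crude comparison.

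**Working it through.** **1. The plan's own figure.** Take 8% vs 4% (the stated 7.9% and 4-point reduction, rounded), two-sided alpha 0.05, 80% power, 1:1 allocation, pooled variance:

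n = [1.960 × √(2 × 0.06 × 0.94) + 0.842 × √(0.08 × 0.92 + 0.04 × 0.96)]² / 0.04² = (0.658 + 0.282)² / 0.0016 ≈ 552.2

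With continuity correction: (552.2 / 4) × [1 + √(1 + 4 / (552.2 × 0.04))]² ≈ 601.1, rounded up to 602. The stated 602 per group reproduces, as the size for an unstratified two-proportion test.

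**2. How conservative the crude test is.** Let w be the stratum weights, p the stratum rates and P = Σwp. Under the null hypothesis, with arms balanced within strata, the true variance of the contrast is a fraction v of what the crude test assumes:

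v = 1 − Σw(p − P)² / [P(1 − P)], and true type I error ≈ 2 × [1 − Φ(1.96 / √v)].

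The documents give neither rates nor weights by RCRI level, so all four gradients below are assumptions, chosen to show a range:

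- Mild: weights 50/30/15/5%, rates 6/8/11/16%.
- Moderate: weights 30/40/20/10%, rates 3/6/12/15.5%.
- Middle: weights 50/30/15/5%, rates 4/8/15/30%.
- Steep: weights 40/35/15/10%, rates 2/6/15/27.5%.

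Example (middle): P = 0.0815, so P(1 − P) = 0.07486. The between-stratum variance is 0.00395, so v = 1 − 0.00395 / 0.07486 = 0.947. Then 1.96 / √0.947 = 2.014, and the type I error is about 0.044.

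**3. Simulation.** 602 per arm, arms balanced within strata, at least 400,000 trials per row. The treatment effect is a halving of risk (mild, middle) or the common odds ratio that takes 7.9% to 3.9%, which is 0.47 (moderate, steep).

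| Gradient | v | Type I, formula | Type I, crude (simulated) | Type I, CMH (simulated) | Power, crude | Power, CMH | Loss (points) |
|---|---|---|---|---|---|---|---|
| Mild | 0.991 | 0.049 | 0.049 | 0.050 | 83.4% | 83.6% | 0.2 |
| Moderate | 0.974 | 0.047 | 0.047 | 0.050 | 80.5% | 81.0% | 0.6 |
| Middle | 0.947 | 0.044 | 0.043 | 0.050 | 85.2% | 86.1% | 0.9 |
| Steep | 0.916 | 0.041 | 0.040 | 0.050 | 81.1% | 82.9% | 1.8 |

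Losses are taken before rounding. A mild gradient can cost as little as 0.1 point, and the loss goes to zero as the gradient flattens.

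**4. Troponin assay.** Assume a 50/50 mix of 7.9% and 17%. The between-assay variance is [(0.17 − 0.079) / 2]² = 0.00207, and the total is 0.1245 × 0.8755 = 0.1090, so assay accounts for 0.00207 / 0.1090 = 1.9% of the variance. Assay is not a randomization stratum, so the simulation must leave its balance to chance. With a risk ratio of 0.65, the crude type I error is then 0.050. Power is 70.5% crude and 71.1% stratified by assay, a gain of about 0.6 points.

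**5. Events available for stratification.** 602 × 0.08 + 602 × 0.04 = 48 + 24 = 72 expected events.

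**The case against.** The strongest reply is that the loss is small and the crude test is sound. It keeps type I error at or below 5%, and in every row above it exceeds the planned 80% power. The sample size was computed for an unstratified comparison, so sizing and test agree. The Discussion describes low-to-mid-risk patients, so high-rate RCRI strata are likely to be small and the steep gradient may be unrealistic. All of this stands, and it limits the point to a small improvement.

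It can also be said that the test list is generic, that RCRI does appear as a subgroup factor, and that an article commonly leaves covariate adjustment to the full plan. This stands in part: a fuller plan may already stratify. But the article says that it reports the analysis plan and offers no other method for a binary outcome, so the point concerns a stated method and not a silence. A subgroup analysis does not adjust the overall comparison.

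Two stronger readings are tempting. A reader might infer that, because the planning incidence rises by a factor of 17 / 7.9 = 2.15 with the assay, chance imbalance in assay biases or invalidates the crude comparison. It does not: randomization leaves that imbalance to chance, and the test's sampling error already covers it (step 4). The two incidences also come from different cited sources and are not observed strata of this trial. A reader might also infer that each center uses a single assay and that assay type is already captured. The article states neither.

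**Conclusion.** The point holds as a minor mismatch between design and analysis. Randomization uses RCRI and the named test for the primary outcome does not. The crude test is valid but mildly conservative. At 602 per arm its true type I error is about 0.040 to 0.049, and the power loss is about 0.1 to 1.8 points. These figures rest on assumed RCRI gradients and weights and on arms balanced within strata; the documents supply no rates by RCRI level. Nothing here makes a significant result untrustworthy. Troponin assay is a separate and optional matter, worth under about one power point on an assumed 50/50 mix.

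**What to change.** State, before any unblinded comparison, that the primary analysis is a Cochran-Mantel-Haenszel test with a stratified risk difference and 95% confidence interval, stratified by RCRI category as randomized. Name the same test for the interim look. Keep the crude chi-square or Fisher's exact test as a supportive analysis.

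Optionally, prespecify assay type (conventional or high-sensitivity troponin T) as an additional prognostic covariate, after confirming that the case report form records it. Do not stratify the primary test by center: with about 72 expected events and a number of centers that the article does not give, strata could become sparse.

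The cost is wording only. No extra patients are needed, and RCRI must be known at randomization, so it needs no new data.

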### Safety monitoring

An independent Trial Oversight Committee has been established, consisting of independent clinicians who have experience in clinical monitoring devices and in the conduct, monitoring, and analysis of data from randomized trials. A single interim analysis will be performed when a number of patients equal to two-thirds of the predefined sample (843/1265) are randomized and completed the outcome up to hospital discharge. We will consider as early stopping criteria a predetermined 2-sided *p* value < 0.01 for the rejection of the null hypothesis that the two BP monitoring strategies are equivalent in terms of primary outcome rate.

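### Interim rejection at p<0.01 combined with a final test at the full 0.05 does not hold the overall error at 5%; the excess is small (up to 5.26%)

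*Protocol article*

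**What the plan says.** Three sections of the protocol article bear on the point.

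- **Safety monitoring** sets the look: "A single interim analysis will be performed when a number of patients equal to two-thirds of the predefined sample (843/1265) are randomized" and have outcomes up to hospital discharge. The boundary follows: "We will consider as early stopping criteria a predetermined 2-sided *p* value < 0.01 for the rejection of the null hypothesis". The hypothesis concerned is the one on the primary outcome rate. Despite the section title, this is a rejection rule for efficacy.
- **Statistical method, analysis strategy, subgroup analysis** says: "All statistical tests will be two-sided and assume a significance α-level of 0.05". No exception is made for the final primary test. The same section offers chi-square or Fisher's exact test for discrete variables and does not say which applies to the primary outcome, or whether chi-square is continuity-corrected.
- **Sample size** gives 602 per group for 80% power to detect a 4-point reduction "in the primary outcome rate in either the C-NIBP or I-NIBP group, with an alpha level of 0.05".

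The article does not lower the final level or name a spending function or group-sequential boundary.

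**The concern.** Two opportunities to reject one hypothesis use more alpha than either alone. If the interim may reject at 0.01 and the final test then uses the whole 0.05, the combined chance of a false rejection is above 0.05 at nominal levels. The protocol would then claim a 5% error rate that its own decision rules do not guarantee.

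The practical consequence is narrow: a final p between about 0.047 and 0.05 would be declared significant when a properly spent final level would not allow it. This is nevertheless the trial's only primary test, and the level is best fixed before data are seen, because a later change could look driven by the result.

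**Working it through.** **Inputs.** Interim at 843 of 1265, boundary two-sided 0.01 (Safety monitoring). Final level two-sided 0.05 (Statistical method). Control rate 7.9%, 4-point absolute reduction, 80% power, alpha 0.05, 602 per group, 1265 enrolled (Sample size). Allocation 1:1 (Assignment of interventions).

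**1. Reproduce the plan's own sample size.** Take 8% vs 4% (the 7.9% rounded, halved), with mean rate 0.06 and difference d = 0.04.

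- Uncorrected: n = [1.960·√(2·0.06·0.94) + 0.842·√(0.08·0.92 + 0.04·0.96)]² / 0.04² = 552.2, so 553 per group.
- Continuity-corrected: n/4·[1 + √(1 + 4/(n·d))]² = 601.1, so **602** per group, total 1204, as stated.
- 1204 × 1.05 = 1264.2, so 1265, as stated.
- With the unrounded 7.9% vs 3.9%, the corrected formula gives 593.

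The stated figure is therefore reproduced at an unadjusted alpha of 0.05 with a continuity correction.

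**2. Overall type I error of the stated rules.** Information fraction t = 843/1265 = 0.666. Under the null the interim and final statistics are bivariate normal with correlation √0.666 = 0.816. The critical values are 2.576 (p = 0.01) and 1.960 (p = 0.05).

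- P(|Z1| > 2.576 or |Z2| > 1.960) = **0.0526**.
- The overlap of the two rejection regions is 0.01 + 0.05 − 0.0526 = 0.0074, so the interim adds 0.01 − 0.0074 = 0.0026 to the final 0.05.
- If information is counted against the 1204 evaluable patients, t = 843/1204 = 0.700 and the total is 0.0522.

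**3. Final level that restores 5%.** Solving P(|Z1| > 2.576 or |Z2| > c) = 0.05 at t = 0.666 gives c = 1.984, two-sided **0.0472**. At t = 0.700 it is 0.0477 (c = 1.980).

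**4. Check with binomial data.** Null trials were simulated with 421 then 632 patients per arm, counting any interim p<0.01 as a rejection.

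| Test | Null rate 5.9–5.95% | 7.9% | 17% |
|---|---|---|---|
| Chi-square, uncorrected, final 0.05 | 5.29% | 5.28% | 5.26% |
| Chi-square, uncorrected, final 0.0472 | 4.98% | 5.01% | 5.02% |
| Chi-square, continuity-corrected, final 0.05 | 3.9% | 4.1% | 4.4% |
| Fisher's exact, final 0.05 | 4.0% | 4.1% | 4.4% |

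The chi-square rows use 2,000,000 trials each and the Fisher row 400,000. Other runs of the uncorrected test fell between 5.21% and 5.30%.

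**5. Price of the lower final level.** For 8% vs 4% with continuity correction, 80% power at 0.0472 needs 611 per group instead of 602. Equivalently, the power of the final test at 602 per group goes from 80.1% to 79.4%, a loss of 0.7 points. For 7.9% vs 3.9% the requirement at 0.0472 is 602.

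**The case against.** Five points can be made for the plan as written.

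- **The test may absorb the excess.** A reader might infer from the two nominal levels that the trial's actual error certainly exceeds 5%. The document does not support that. Fisher's exact test and a continuity-corrected chi-square are both permitted, and both leave the realised error below 5%. The 602 per group reproduces only with a continuity correction, which hints at a corrected test. This objection stands and limits the claim. It does not remove the defect, because the plain chi-square is equally permitted and error control should not rest on an unstated correction.
- **Stopping is discretionary.** The article says the criterion will be considered. If the committee may continue past p<0.01 and the verdict then rests on the final test, the nominal error lies between 5.00% and 5.26%. This stands: 5.26% is an upper bound under the normal approximation. The criterion is still worded as rejecting the null, so the chance has to be counted unless the plan says the look carries no efficacy claim.
- **The analysis plan may set the final level.** A spending function is often left to that document, which is not shown, and silence here would be no fault. But this article is not silent: it sets 0.05 for all tests. A lower final level elsewhere would contradict that sentence, which would still need changing.
- **A strict interim boundary makes the adjustment negligible.** That is true near 0.001, where the same calculation gives 0.0501. At 0.01 the excess is 0.0026 against about 0.00006.
- **The sample size is adequate.** A reader might also infer that the trial is underpowered once alpha is corrected. That does not follow: on the documented 7.9% vs 3.9%, 602 per group is what 0.0472 requires. The match does not show that an adjustment was made, since the stated alpha is 0.05.

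**Conclusion.** The stated rules do not guarantee the stated 5%. With an interim boundary of 0.01 at information fraction 0.666 and a final level of 0.05, the overall two-sided type I error is up to 5.26%, an excess of about 0.26 percentage points. This rests on three assumptions: an uncorrected chi-square test, every interim p<0.01 counted as a rejection, and information proportional to patients. Under a continuity-corrected chi-square or Fisher's exact test the realised error is about 3.9% to 4.4%, so the documents do not show that the trial will in fact exceed 5%. The point is a minor but real error in what the protocol fixes. It does not threaten the trial's power or the estimate of effect.

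**What to change.** - In Safety monitoring, keep the single interim boundary at two-sided p<0.01 and say whether crossing it counts as rejection of the primary null hypothesis.
- In Statistical method, state that the final primary analysis is tested at two-sided 0.047 (|z| ≥ 1.984) with the matching 95.3% confidence interval, and limit the general 0.05 sentence to the other tests. Alternatively, take both boundaries from one named alpha-spending function, which would also cope with an interim that does not fall exactly at 843 patients.
- Name the primary test and say whether it is continuity-corrected.
- In Sample size, restate the power at the final level.

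The cost is a few sentences and no extra patients. The 0.7-point loss in step 5 concerns the final test alone. Trials already rejected at the interim are unaffected by the lower final level, so the loss for the whole design is less than about 0.7 percentage points.
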